**Fig. 1 Fig1:**
[figure not shown]
The schedule of enrollment, interventions, and assessments of the HWePS program

### Study setting and participants

The HWePS is being conducted in two urban neighborhoods (*dong*; 1 intervention *dong*, 1 control *dong*) within Jungnang-gu in Seoul, Korea. Jungnang-gu, one of the easternmost districts of Seoul, is home to a higher-than-average proportion of older adults living alone (8.7% vs. 7.1% in Seoul) and people receiving national basic livelihood security (7.0% vs. 4.1% in Seoul). Out of the 25 districts in Seoul, Jungnang-gu has the third lowest fiscal independence rate as of 2020 [33]. The intervention and control areas (*dong*) within Jungnang-gu have similar proportions of older residents, but they are geographically remote from each other in order to prevent any spillover effect. The selection of these particular neighborhoods was also based on health statistics about the areas as well as input from the public health center in Jungnang-gu regarding service needs in the intervention areas.

Study participants include older adults residing in the intervention and control areas who consent to participate in the research study. Participants come from a pool of individuals who participated in a community-wide community health and wellness survey conducted in late 2020 [34]. Inclusion criteria for participants are as follows: 1) aged 65 or older, 2) non-frail based on the K-FRAIL [35], 3) not a long-term care insurance beneficiary, and 4) not planning to move away from the area during the intervention period. Study participation is entirely voluntary, and participants may withdraw from the study at any time.

### Intervention

#### Components of the HWePS

Health literacy intervention based on individual- and community-needs assessment

The HWePS aims to increase personal and also community health literacy through a community-wide, multi-channel health information delivery service and individualized self-checkups of functional capacity. The former aims to increase the access of community residents to valid and reliable heath information tailored for the information needs of the community during COVID-19, when community health and social services are closed or largely reduced. The contents of the health information service have been curated based on a needs assessment via a community-wide health and wellness survey in late 2020 [34] and other relevant reports/statistics, as well as various input obtained during the intervention development process from residents, community leaders, clinical professionals, and health and administrative officers in the community. The evidence-based contents cover a wide range of health information aiming to prevent frailty and promote healthy aging, including suggestions for improving physical activity, nutrition/diet, mental health, social relationships, and safety measures related to COVID-19. This health information is delivered regularly via SMS as an e-poster or via postal mail according to each older person’s preference. The information delivery service is augmented by weekly in-person or phone counseling provided by community nurses, an optional service for anyone who would like to ask questions for a better understanding of the delivered information and/or seek further information and services.

The self-checkup is a decision-support service that aims to help older persons assess and be aware of their own strength, weakness, and risk factors in maintaining and promoting functional capability [3]. The self-checkup service is a smartphone application-based, multi-dimensional functional assessment tool using the interRAI Check-Up Self-Version (CUSR) and other intervention-relevant items. The CUSR is a valid and reliable self-assessment tool designed to examine the health and functional status of relatively healthy community-dwelling residents by themselves or with the assistance of family members/lay helpers [27, 36]. Upon completion of a 90-item health check-up, the CUSR generates a report including key function scales and a list of clinical assessment points for common geriatric health risks (e.g., pain, falls, inactivity, smoking/drinking, nutrition, cardiovascular disease, etc.) using triggers derived from evidence-based algorithms. The self-checkup experience is expected to motivate older persons to seek appropriate health information and services relevant to their own health risks, empower them to make a self-care plan, become interested in self-care skill-building activities, and practice a healthy lifestyle, all which are the contents of the (self-)care management component of the HWePS described below.2.Personalized care management featuring nurse coaching and peer support

The personalized care management grounded on self-checkup results is based on the SPEC intervention model [20, 25]. It features care planning with a nurse coach and self-care skill-building with peer support. Care planning with a nurse coach is a critical component of the HWePS to empower each older person to develop their own action plan to build their self-care capacity reflecting their own preferences, choices, and timeline for health promotion goals, action plans, and activities. Older participants execute daily self-directed care plans with the guidance and support of a nurse-led multidisciplinary care team along with trained community lay health leaders (CLHLs). The multidisciplinary care team consists of a lead nurse, nurse coaches, a fitness specialist, a nutritionist, and a social worker. The nurse coaches are community health nurses (CHNs) for the “visiting community service center service” program in the intervention neighborhood who are trained for this role; in addition, a CHN will take on the role of lead nurse during the dissemination phase of the intervention. Based on the results of the individualized needs assessment, the nurse coach follows evidence-based protocols to guide older adults’ care plans and guides CLHLs to provide peer support assisting older adults to reach desired goals and outcomes.

The care management program is a 12-week, self-care skill-building, multidisciplinary, tailored intervention with peer support from trained CLHLs. At the beginning of the care management intervention, a self-checkup using the CUSR is conducted by each older participant with the support of a trained CLHL (a peer in the community) through an interview; the CLHL assists the older person to read the CUSR items and/or fill out the electronic questionnaire. Upon completion of the CUSR, the CLHL reviews the automated report and assessment results with the participant and delivers 1- to 2-page educational pamphlets describing each of the identified health risks derived from a total list of common geriatric health issues. The care management process involves the assignment of a nurse coach; reviews of older adults’ health needs and preferences as determined by the CUSR and social and literacy items from the community health and wellness survey; goal setting; personalized health information; and delivery of tailored exercise, nutrition, mood, and social intervention programs, along with a 12-week program promoting walking and other physical activities. Using the HWePS app, older adults can set their own tasks toward achieving their health goals, and CLHLs provide peer support to empower and strengthen older people’s self-care capacity using the app’s to-do checklist set by the older adult. In addition, multidisciplinary care conferences (MCCs) are held for more in-depth team discussions on care planning and coordinated delivery for complex or especially vulnerable older adults. During an MCC, the initial care plan is refined based on in-depth team discussion. If a referral to community resources such as medical or public welfare services is required, a request form is prepared and sent to the relevant institutions.3.A healthy-living and healthy-aging community initiative

The importance of addressing upstream social determinants of health has been emphasized for reducing health inequity [37]. Guided by the BARHII and the ECCM models [19, 23], the HWePS goes beyond individual-level care planning to develop community-wide healthy living conditions promoting healthy aging. Various community participatory activities (CPAs) exist under the community-wide initiative, aiming for 1) creating a supportive environment, 2) strengthening community capacity, and 3) building community resources/networks [19]. The CPAs, which seek to create a supportive living environment in which older adults can pursue a healthy life, include services and programs such as age-friendly smartphone subscriptions, smartphone education, and home installation of safety bars for high-risk groups. “Strengthening community capacity” is a component that develops the community’s health-oriented capabilities to utilize local resources and enables community members to identify and solve local health problems on their own. The CPAs include community health-education sessions and training CLHLs as health activists in the community. The CLHLs include people over 50 years of age residing in the intervention area and serve as key players in delivering the HWePS model within the community. Lastly, building community resources/networks involves organically connecting the various health care and welfare services that are segmented within the community and making referrals to participants as needed. Through regular meetings, research teams collaborate with various stakeholders to continuously identify local needs, search for and find relevant human and material resources, build strategic partnerships within the region to develop a myriad of community-level resources and networks, and develop and implement new services and programs together.

These CPAs under the healthy-living, healthy-aging community initiative aim to address older adults’ social determinants of health by building a foundation to empower the community’s health efficacy. Participating stakeholders include the researchers and the multidisciplinary intervention team as well as local stakeholders including older residents, community leaders, health and social professionals, civic groups, and the advisory committee. Monthly meetings are held with local public health stakeholders to identify existing community resources to which referrals may be made and to solidify new partnerships and integrate them into the community. The newly developed community-level healthy aging programs and services are managed by the senior health and wellness center, and individual referrals are made by the multidisciplinary care team members as required.4.Information and communications technology (ICT) systems

HWePS includes a multi-channel health information service for older participants that mainly delivers information as an e-poster via KakaoTalk, a multifaceted, free SMS application. For those without a smartphone or who lack the relevant digital literacy, printed information packets are delivered by postal mail. For personalized care management, a prototype HWePS information system has been developed for research purposes, including a smartphone application (hereafter the HWePS app) for end users (seniors, lay leaders, health professionals) and a cloud-based website for managers (health professionals, the research team). The HWePS information system includes modules for self-checkups and needs assessments; care planning and monitoring; education; and community resources for older adults, lay leaders, and/or health professionals. These ICT tools facilitate online communication between seniors, lay leaders, professionals, and the research team, which is especially helpful for implementing the HWePS program during COVID-19. Furthermore, the cloud-based system allows for real-time access to collected data, facilitating communication between members of the care team and the research team. Throughout the intervention, the research team also actively utilizes KakaoTalk for various purposes including progress checks on intervention delivery and/or data collection and reminders. Further details on all the HWePS intervention components are summarized in Table 1.

**Table 1 Tab1:** Description of the HWePS intervention: components, theoretical rationale, aims, and implementation information

Component	Theoretical Rationale	Detailed Intervention Description	Specific Aim	Intervention Level
1. Health literacy intervention based on both community and individual needs assessments	- ECCM: Decision support - Comprehensive HL intervention model	- Community-wide, multi-channel health information delivery service (SMS or postal mail) based on a community health survey and other relevant reports/documents related to community health needs - Individualized needs assessment using interRAI CUSR producing health and functional profiles and risk triggers based on evidence-based algorithms	- Promote health literacy for older people, community lay health leaders (CLHLs), and the care team - Increase health awareness - Facilitate communication between the community and the public health center (the intervention team)	-Individual -CLHLs (peers) & health professionals - Community
2. Personalized (self-)care management with a nurse-led multidisciplinary team and peer support by community lay health leaders (CLHLs)	- ECCM: Self-management; developing personal skills; delivery system design - SPEC intervention model	- Self-care planning by older people with a nurse coach, based on the CUSR report - Features nurse coaching for self-care goal setting and skill-building education/planning, and peer support (by trained CLHLs) for keeping to the plan - Tailored intervention and information (SMS) programs for one or more triggered/preferred healthy life-style areas (diet, exercise, mood, and social relationship) by multidisciplinary care team - Community-wide walking promotion program - Nurse-led multidisciplinary care conferences (MCCs) attended by both professionals and CLHLs	- Enhance self-care of identified health problems - Improve health behaviors through self-care and coaching from care team and CLHLs - Improve health outcomes and efficacy through self-care and walking promotion - Increase easily accessible resources within the community as a window for health needs and referrals - Strengthen social support in the community	Individual
3. Healthy-living and healthy-aging community initiative	- ECCM: Creating supportive environments; strengthening community capacity; building community resources, networks & partners - BARHII Framework	- Activities for creating supportive environment (e.g., smartphone subscription program, smartphone education, safety-bar installation for high-risk households) - Activities for strengthening community capacity (e.g., community health education sessions, CLHL training) *-* Activities for building community resources/networks and community partners^a^ (e.g., referrals to community center nurse, social welfare center, medical center)	- Improve living conditions for healthy aging, in particular, health and social care service conditions - Address HRSNs and social determinants of health	Community
4. HWePS information and communications technology (ICT) system	- ECCM: Information systems - SPEC intervention model	- Use of the HWePS project smartphone application (the HWePS app, for research purposes) and a cloud-based website for care management - Use of KakaoTalk for communication between research team, multidisciplinary care team, CLHLs, lay assessors	- Promote effective and efficient information exchange and communication between players - Collect and store electronic data in a secured information system	-Individual - CLHLs (peers) & health professional - Community

*ECCM* The extended chronic care model [19], *HL* Health literacy model [21], *SPEC* The System for Person-centered Elderly Care [25], *BARHII* The Bay Area Regional Health Inequities Initiative [23], *HRSN* Health-related social needs, *CLHL* Community lay health leaders, *SMS* Short message service, *MCC* Multidisciplinary care conference

^a^Community partners include local health and social care providers, NGOs, public health centers, community service centers, Jungnang district office, the health promotion department of the City of Seoul, etc.

In summary, participants in the intervention area will receive the entirety of the HWePS intervention comprising a health literacy intervention including a community-wide, multichannel, health information delivery service and individualized self-checkups; a 12- week, technology-enhanced care management program for care planning and self-care skill-building through nurse coaching and peer support; and a community-wide initiative promoting healthy aging and aiming in particular to address living conditions and health/social care service conditions, midstream/upstream causes of health inequality, by integrating a wide range of services meeting health and health-related social needs. All services are arranged and based in a senior health-wellness center, the basecamp for the intervention team, located at a five-minute walk from the community service center in the intervention area. The wellness center also coordinates delivery of small prizes (e.g. food packages for nutrition, exercise equipment, personal hygiene amenities, etc.) for older adults in the tailored programs to encourage ongoing participation throughout the intervention period.

During the entire intervention period, the participants in the control area will receive a community-wide health information delivery service, which is a part of the literacy intervention. Delivery of the health information will be carried out identically to the intervention group through KakaoTalk (an SMS program widely used in Korea), or postal mail. Other than receiving health information, the control region will not receive any other components of the intervention, such as individualized needs assessments through self-checkups using the CUSR, tailored care planning, or community-level healthy aging capacity-building and empowerment.

### Outcomes

The study seeks to evaluate two primary outcomes: self-rated health and health-related quality of life (HRQoL), along with several secondary outcomes and process evaluation measures. Most primary and secondary outcomes are taken from the annual Community Health Survey, a nationwide survey conducted by the Korean CDC [38]; outcomes from other sources are indicated accordingly. All outcomes and their measurements are summarized in Table 2.

**Table 2 Tab2:** Overview of the outcome variables, measures, and observation points

Outcome	Variable	Data Source/Instrument	Measurement Points	Target Respondents
Primary	Self-rated health	WHO World Health Survey; Korea Community Health Survey	T1, T2	IG, CG
	Health-related quality of life	EuroQol (EQ)-5D-3L	T1, T2	IG, CG
Secondary	Frailty	Fried’s frailty phenotype	T1, T2	IG, CG
	Wellbeing	World Health Organization- Five Well-Being Index (WHO-5)	T1, T2	IG, CG
	Self-efficacy	Korean Self Rated Abilities for Health Practices (K-SRAHP)	T1, T2	IG, CG
	Community efficacy	Collective Efficacy Scale	T1, T2	IG, CG
	Physical activity	Korean version of the International Physical Activity Questionnaire (K-IPAQ) as presented in the Korea Community Health Survey	T1, T2	IG, CG
	Hypertension awareness, diabetes awareness, mood, stress	Single items taken from the Korea Community Health Survey	T1, T2	IG, CG
	Functional health	Scales and CAPs from interRAI Check-Up Self-Rated Version (CUSR)	T1, T2	IG
	Technology acceptance	Short version, Senior Technology Acceptance Measure (STAM)	T1, T2	IG
	Nutrition, depression	Nutrition Questionnaire Elderly (NQE), Patient Health Questionnaire-9 (PHQ-9)	T1, T2	IG participants who received tailored programs
	Satisfaction	Client Satisfaction Questionnaire	T2	IG

*IG* Intervention group, *CG* Control group

#### Primary outcome measure

*Self-rated health* is measured with a single item that asks, “In general, how do you consider your overall health?” using a 5-point scale (1 = Very good; 5 = Very poor). Self-rated health is a widely-used measure of subjective morbidity [39], which has been validated in various settings including for health-equity analyses [40]. *HRQoL* is measured using the Korean version of the EuroQol-5 Dimensions, three-level version (EQ-5D-3L), a widely-used standardized measure of health-related quality of life with good reliability and validity across international samples [41]. The EQ-5D-3L assesses five dimensions of health (mobility, self-care, usual activity, pain/discomfort, and depression/anxiety), and each domain is rated from 1 to 3, with 1 meaning no problems, 2 meaning some problems, and 3 meaning extreme problems.

The primary outcomes will be measured at two time points: at T1 (Week 0; upon enrollment) and T2 (Week 13; following the end of the 12-week personalized intervention period).

#### Secondary outcome measures

*Frailty* will be measured using Fried’s frailty phenotype [42], composed of five domains: weakness, slowness, exhaustion, low physical activity, and unintentional weight loss. Weakness and slowness are performance-based items, assessed by grip strength and gait speed respectively, adjusted for gender and body mass index/height. Grip strength is measured using the CAMRY EH-101 electronic hand dynamometer, and gait speed is measured using a tape measure of 2.5 m. Exhaustion, low physical activity, and weight loss are derived from survey-based self-report items. Each component is scored 0 or 1 with a final score of 0 (healthy) to 5 (frail).

*Wellbeing* is measured using the WHO-5 Well-Being Index (WHO-5), a short questionnaire that assesses the subjective well-being of patients. Each item is rated from 5 (always) to 0 (never), and the sum score of all items is utilized. The WHO-5 has been translated into Korean with acceptable reliability (0.83) [43].

*Self-efficacy* will be measured using the Korean Self-Rated Abilities for Health Practices (K-SRAHP) health self-efficacy measure [44]. The measure, based on Becker et al.’s (1993) health self-efficacy scale [45], has been revised and tested for validation in a Korean sample [44]. A total of 24 items of health self-efficacy covering 6 domains (physical activity, disease management, emotional regulation, nutrition, stress management, and health behavior) are measured and rated on a 5-point scale from 0 (not at all) to 4 (completely). A composite score of 0 to 96 is utilized for the analysis.

*Community efficacy* of the residential area is measured using five items that have been revised based on Sampson et al.’s (1997) Collective Efficacy Scale [46] to better reflect the Korean situation [47]. Collective efficacy is measured by two sub-concepts, informal social control and social cohesion/trust. The five items are measured on a 5-point scale ranging from 1 (strongly agree) to 5 (strongly disagree) and reverse-coded so that larger values indicate greater collective efficacy. The reliability of the five items has a Cronbach’s alpha of 0.681 [47].

*Physical activity* is measured using the Korean version of the International Physical Activity Questionnaire (IPAQ) short form [48]. The IPAQ is a self-reported measure that assesses the amount of physical activity (vigorous, moderate, walking, sitting) performed over the past 7 days. The IPAQ is used to compute respondents’ *moderate to high exercise rate* (more than 20 min of vigorous physical activity, 3 or more days a week OR more than 30 min of moderate physical activity, 5 or more days a week) and *walking practice rate* (more than 30 min of walking, 5 or more days a week), using algorithms from the Korean Community Health Survey [38].

*Hypertension awareness*, *diabetes awareness, mood,* and *stress* are all secondary outcomes measured by single items from the Korean Community Health Survey [38]. *Hypertension awareness* and *diabetes awareness* seek to assess whether the respondent is aware of their blood pressure and sugar levels, both indicators that can influence healthy lifestyles [49]. *Mood* is assessed by the yes/no question, “In the past 1 year, have you experienced sadness or hopelessness that interferes with your daily life for two or more consecutive weeks?” *Stress* is measured by 4-point scale in response to a question that asks how much stress the respondent experiences in his/her daily life (1: very much – 4: not at all). The item is dichotomized into experiencing stress [1, 2] and not experiencing stress [3, 4].

*Technology acceptance* is measured with the short version of the Senior Technology Acceptance Measure (STAM), which was developed based on the Technology Acceptance Model [50]. The STAM is a 14-item, self-rated questionnaire using a 10-point Likert scale, and it consists of 4 domains as follows: attitudinal beliefs, control beliefs, gerontechnology anxiety, and health. There was no existing STAM questionnaire in Korean, so with the approval of the instrument developer group [50], a Korean version of the STAM was developed through forward- and back-translation guided by the process of translation and adaptation of research instruments of Chen et al.

*Functional health* is assessed from the scales and clinical action points (CAPs; e.g., falls, cardiovascular disease, pain, etc.) in the interRAI Check-Up Self-Report (CUSR) [27]. The interRAI CUSR is a multidomain geriatric assessment to screen older adults’ intrinsic capacity, designed to be administered by themselves and/or with assistance from non-health professionals in the community or primary care setting. The CUSR has good psychometric properties in other countries [27, 36] and also in Korea [34].

*Nutrition* and *depression* are measured for those who receive tailored intensive intervention programs (nutrition, emotional). For those who participate in the intensive nutrition program, the Nutrition Quotient for Elderly (NQ-E) is used to measure the nutritional status and dietary quality of older adults [51]. The NQ-E assesses nutritional status through 19 items across four domains (balance, variety, restriction, dietary behavior), which are weighted and summed to determine the respondent’s nutrition rating: low, medium–low, medium–high, or high. For those who participate in the intensive emotional program, the PHQ-9 is used to measure depression. The PHQ-9 comes from the Patient Health Questionnaire developed by Kroenke et al. [52] and translated into Korean by Han et al. [53]. The Korean version of the PHQ-9 has good internal consistency (0.88) and convergent validity (0.74).

*Program satisfaction* is collected using a modified version of the Client Satisfaction Questionnaire, with 8-items that evaluate the participants’ program satisfaction. The measure, which has been translated by Hwang [54], is widely used for Korean public programs.

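### The four-level stress item is cut to yes/no for analysis, which discards information; the size of the loss depends on a response distribution the article does not give.

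*Protocol article*

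**What the plan says.** Protocol article, Secondary outcome measures. Stress is a single Community Health Survey item on "how much stress the respondent experiences in his/her daily life", answered on four ordered levels ("1: very much – 4: not at all"). The article then states: "The item is dichotomized into experiencing stress [1, 2] and not experiencing stress [3, 4" (levels 1–2 against 3–4).

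The same section describes the IPAQ short form as an instrument that "assesses the amount of physical activity (vigorous, moderate, walking, sitting) performed over the past 7 days". The article names two quantities derived from it, both yes/no rates built with the national survey's algorithms. One is a moderate-to-high exercise rate; the other is a walking rate defined as "more than 30 min of walking, 5 or more days a week".

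Other graded measures are not cut. The WHO-5 is used as a sum score and the health self-efficacy measure as a 0 to 96 composite. No cut is stated for the 5-point self-rated health item, for which Table 2 also lists the Community Health Survey as a source.

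The Data analysis plan (Effect evaluation) names mixed effects models and GEE but does not assign a scale to each outcome. Walking is part of the intervention: Components of the HWePS describes tailored programmes delivered "along with a 12-week program promoting walking and other physical activities".

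**The concern.** Merging levels 1 with 2 and 3 with 4 makes a move from very much stress to the next level, or from level 3 to not at all, invisible to the arm comparison. The stress cut is a stated rule, not a detail left to another document. Both arms answer the same item at T1 and T2, so comparing the two neighbourhoods does not require the cut. At stake is precision on one secondary outcome: a wider interval and a greater chance of an inconclusive result than the collected data warrant.

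The activity rates raise a milder form of the same issue. A threshold rate does not register change that stays on one side of the threshold, and walking is a behaviour the programme promotes directly. The Walk-On app logs are to be analysed descriptively for the process evaluation, so of the sources the article describes, the IPAQ is the one that carries a between-arm comparison of walking.

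**Working it through.** **Inputs from the article.** Four ordered stress levels; cut at {1,2} against {3,4}; secondary outcome. The article gives no power or expected distribution for stress, so there is no plan figure to reproduce. The 265 per arm under Sample size and recruitment was set for self-rated health.

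**Inputs assumed.** The shares p1 to p4 of answers in the four levels.

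**Formula.** Under proportional odds, information on the log odds ratio is proportional to (1 − Σp³)/3 for the four-level item and to b(1 − b) for the binary item, where b = p1 + p2. Relative efficiency is therefore

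RE = 3b(1 − b) / (1 − Σp³), and the information lost is 1 − RE.

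Worked case, equal quarters: Σp³ = 4 × 0.25³ = 0.0625; RE = 3 × 0.25 / 0.9375 = 0.80; loss 20%.

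**Power translation.** If the ordinal analysis had 80% power (two-sided 5%), the binary analysis has power Φ(2.802·√RE − 1.960), where 2.802 = 1.960 + 0.842. For equal quarters this is Φ(2.802 × 0.894 − 1.960) = Φ(0.546) = 71%.

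| Assumed split, levels 1/2/3/4 (%) | b | 3b(1−b) | 1−Σp³ | RE | Loss | Sample-size factor 1/RE | Binary power if ordinal has 80% |
|---|---|---|---|---|---|---|---|
| 25/25/25/25 | 0.50 | 0.750 | 0.938 | 0.80 | 20% | 1.25 | 71% |
| 5/20/45/30 | 0.25 | 0.563 | 0.874 | 0.64 | 36% | 1.55 | 61% |
| 3/15/50/32 | 0.18 | 0.443 | 0.839 | 0.53 | 47% | 1.89 | 53% |
| 5/45/45/5 | 0.50 | 0.750 | 0.818 | 0.92 | 8% | 1.09 | 77% |
| 2/8/50/40 | 0.10 | 0.270 | 0.810 | 0.33 | 67% | 3.00 | 37% |

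The last two rows mark the ends of the range examined. The loss is small when most answers sit in the two middle levels, and large when few respondents are in levels 1–2.

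**Cross-check with another model.** With equally spaced scores and a latent normal shift, the loss is 26% for equal quarters, 22% for 5/45/45/5 and 56% for 2/8/50/40. The direction is the same and the range somewhat narrower.

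**Simulation, illustrative only.** Assumptions: 265 per arm, T1–T2 correlation 0.5, latent shift 0.25 SD, independent participants, and each analysis adjusted for its own T1 value. For the first three splits, power is about 78–85% on the 4-point score. On the cut item it is about 67–68%, 54–58% and 45–51% respectively. For 5/45/45/5 it falls from 81% to 66%, more than the 8% loss suggests, because the T1 adjustment is dichotomised too.

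**Walking.** Let the indicator be 1 if the participant has five or more qualifying days. A change from 0 to 4 days goes from 0 to 0 and is not registered. A change from 4 to 5 days goes from 0 to 1 and is registered in full. A change from 5 to 7 days goes from 1 to 1 and is not registered. This follows from the definition alone. No gain in power is calculated, because the article gives no distribution of walking days or minutes.

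**The case against.** **The size is not known for this trial.** A reader might take 20–47% as the loss the trial will suffer. The documents do not support that: no stress distribution is given, and the larger figures come from splits that put 25% or 18% of respondents in levels 1–2. Splits concentrated in the middle lose far less. The simulated powers also rest on a 0.25 SD shift that appears nowhere in the article. They ignore the design of one neighbourhood per arm with 15 *tongs* in each, and fit a linear score model rather than the cumulative-logit model recommended here. This objection stands in full. What survives is the direction, and a size given as a range over assumptions. Proportional odds is itself an assumption: if the effect sat entirely at the boundary between levels 2 and 3, the cut would lose little.

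**For activity, exclusive use of the rates is an inference.** The article says what the IPAQ is used to compute; it does not rule out a graded analysis in a fuller plan. The rates can be called the only measures this document names, and no more.

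**The thresholds serve a purpose.** The activity cut-offs are taken deliberately from the national survey, and the team plans dissemination within the district and city. Meeting a walking threshold is a legitimate public-health quantity, so choosing it is a choice of estimand rather than an error. It would be tempting to say that nothing is given up by replacing the rates. That is not so: an ordinal or day-based effect is harder to set beside published survey rates. This is why the rates should keep a place in the comparison.

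**Stress is not a named target.** A reader might infer that the programme aims at stress as directly as at walking. The tailored areas listed are exercise, nutrition, mood and social relationships. Mental-health content belongs to the information service that both arms receive.

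**Conclusion.** The point holds for stress, as a modest one. The article fixes a two-category analysis of a four-level item, and this discards information in the arm comparison. The proportional-odds loss is 20% with equal quarters, about 36% with 5/20/45/30%, about 47% with 3/15/50/32%, and about 8% to 67% over the wider set of splits. Every one of those splits is an assumption.

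For physical activity, the finding is limited to a property of the named rates: they do not see change that stays on one side of the cut. The documents do not show that a graded analysis would be more powerful, nor that none is planned.

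The article is not contradictory here. Neither primary outcome is affected, and the sample size does not depend on these items. It is a cheap improvement, not a defect that threatens the trial's conclusions.

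**What to change.** - **Stress.** State that arms are compared on the four-level item with a cumulative-logit GEE or mixed model adjusted for the T1 response, with the direction of the odds ratio defined and the proportional-odds assumption examined. Report the dichotomised survey rate by arm alongside it.
- **Physical activity.** Keep the arm comparison on the two Community Health Survey rates. Add a supportive comparison of IPAQ walking days per week, labelled as supportive and without any claim of greater power.
- **Any loss figure quoted** should carry the assumed response distribution with it.

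The cost is plan wording. The graded answers are already collected, and SAS 9.4, the package named in the article, fits these models. Trial status reports that analysis had not begun when the article was submitted; the change should be recorded before outcome data are analysed. The small downside is that the ordinal stress effect is less directly comparable with published survey rates; reporting the rate beside it covers most of that.
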